### Sample size

The primary clinical endpoint is the incidence of infants born with birth weight >4000 grams, with an estimated incidence in women eligible for this trial of 15.5% [12]. To detect a difference from 15.5% to 7.35% (alpha 0.05; power 80%), and accounting for 5% rate of attrition (based on our experience with the LIMIT Study), [12] we will recruit a total of 524 women. This sample size will be powered (80%) to detect the differences in secondary outcomes as detailed in the table below.

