**Methods:**

Design: Multicentre randomised, controlled trial.

Inclusion Criteria: Women with a singleton, live gestation between 10^+0^-20^+0^ weeks who are obese or overweight (defined as body mass index greater than or equal to 25 kg/m^2^), at the first antenatal visit.

Trial Entry & Randomisation: Eligible, consenting women will be randomised between 10^+0^ and 20^+0^ weeks gestation using an online computer randomisation system, and randomisation schedule prepared by non-clinical research staff with balanced variable blocks. Stratification will be according to maternal BMI at trial entry, parity, and centre where planned to give birth.

Treatment Schedules: Women randomised to the *Metformin Group* will receive a supply of 500 mg oral metformin tablets. Women randomised to the *Placebo Group* will receive a supply of identical appearing and tasting placebo tablets. Women will be instructed to commence taking one tablet daily for a period of one week, increasing to a maximum of two tablets twice daily over four weeks and then continuing until birth. Women, clinicians, researchers and outcome assessors will be blinded to the allocated treatment group.

All women will receive three face-to-face sessions (two with a research dietitian and one with a trained research assistant), and three telephone calls over the course of their pregnancy, in which they will be provided with dietary and lifestyle advice, and encouraged to make change utilising a SMART goals approach.

Primary Study Outcome: infant birth weight >4000 grams.

Sample Size: 524 women to detect a difference from 15.5% to 7.35% reduction in infants with birth weight >4000 grams (*p* = 0.05, 80% power, two-tailed).

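### The 524 women said to allow for 5% attrition match the continuity-corrected requirement with no attrition at all

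*Protocol article*

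**What the plan says.** The Sample size section of the protocol article sets the primary endpoint as birth weight above 4000 g, "with an estimated incidence in women eligible for this trial of 15.5"%. It fixes the target as follows: "To detect a difference from 15.5% to 7.35% (alpha 0.05; power 80"%). It then says that, "accounting for 5% rate of attrition (based on our experience with the LIMIT Study), [12] we will recruit a total of 524 women".

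The Abstract (Methods) gives the same total for the same contrast, "524 women to detect a difference from 15.5% to 7.35% reduction in infants with birth weight >4000 grams", with "80% power, two-tailed". It does not mention attrition.

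The Sample size section adds: "This sample size will be powered (80%) to detect the differences in secondary outcomes". The table that follows lists caesarean section (39.1% to 27.2%), induction of labour (36.8% to 25.1%), pre-eclampsia (14.1% to 6%) and gestational diabetes (10% to 3.5%).

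No formula, test, continuity correction or pre-attrition number is given.

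**The concern.** A recruitment target that allows for 5% loss should exceed the number needed for analysis by a factor of 1/0.95. Here the standard continuity-corrected calculation returns the recruitment target itself, with nothing left for loss. If that is how 524 was obtained, the attrition allowance is a property the text claims and the number lacks. The 80% power stated for the primary outcome and for the secondary table would then hold only if every randomised woman contributes an outcome, which the protocol itself does not expect. Readers will rely on the stated power when they interpret a null primary result.

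**Working it through.** **Inputs.** p1 = 0.155, p2 = 0.0735, alpha 0.05, power 80% and 5% attrition come from the Sample size section. The two-sided test comes from the Abstract. Equal allocation is an assumption: the Trial entry section describes two groups in balanced blocks but states no ratio.

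**Step 1: uncorrected number per arm.** With d = p1 − p2 = 0.0815 and mean rate p̄ = 0.11425,

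n = [1.960·√(2p̄(1−p̄)) + 0.8416·√(p1(1−p1) + p2(1−p2))]² / d²

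= [1.960 × 0.44988 + 0.8416 × 0.44618]² / 0.0815² = (0.88175 + 0.37551)² / 0.0815² = 237.98,

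so 238 per arm and 476 in total.

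**Step 2: continuity-corrected number per arm.**

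n_c = (n/4)·[1 + √(1 + 4/(n·d))]² = (237.98/4)·[1 + √1.20624]² = 261.94,

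so 262 per arm and **524 in total**. This is the printed figure, reached with zero loss.

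**Step 3: add 5% attrition, dividing by 0.95 and rounding up.**

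| Method | Total analysed | Total with 5% loss |
|---|---|---|
| Continuity-corrected | 524 | 552 |
| Uncorrected (step 1) | 476 | 502 |
| Unpooled variance | 472 | 497 |
| Pooled variance only | 480 | 506 |
| Arcsine | 464 | 489 |
| Fisher exact (about) | 514 | 542 |

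No entry in the last column is 524 or within 3% of it.

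**Step 4: test the inference against the printed rates.** For each control rate, solve for the treatment rate that gives 80% power.

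| Outcome | Printed | 262/arm, corrected | 249/arm, corrected | 249/arm, uncorrected |
|---|---|---|---|---|
| Birth weight >4000 g | 7.35% | 7.35% | 7.16% | 7.51% |
| Caesarean section | 27.2% | 27.22% | 26.9% | 27.3% |
| Induction of labour | 25.1% | 25.13% | 24.8% | 25.2% |
| Gestational diabetes | 3.5% | 3.49% | 3.35% | 3.68% |
| Pre-eclampsia | 6% | 6.32% | 6.14% | 6.49% |

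The first four rows match the printed values to the precision given only in the column for 262 analysed per arm with correction. Pre-eclampsia is printed as a whole number, and all three columns round to 6%, so it does not discriminate.

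**Step 5: power after the expected loss.** 524 × 0.95 = 497.8, about 498 analysed or 249 per arm. Corrected power is the uncorrected power at the effective size m = (n·d − 1)²/(n·d²). For the primary outcome n·d = 249 × 0.0815 = 20.29, so m = 19.29²/(249 × 0.0815²) = 225.1.

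| Outcome | Corrected power, 249/arm | Uncorrected power, 249/arm |
|---|---|---|
| Birth weight >4000 g | 77.8% | 81.8% |
| Caesarean section | 78.0% | 80.7% |
| Induction of labour | 78.0% | 80.8% |
| Pre-eclampsia | 81.7% | 85.4% |
| Gestational diabetes | 77.6% | 82.6% |

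Fisher exact power for the primary outcome at 249 per arm is 78.8%.

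**The case against.** The best defence is that the article names no test, so the continuity correction is inferred. Under the ordinary uncorrected calculation, 524 does cover 5% loss: every listed outcome keeps at least 80% power at 249 per arm. A recruitment number above the minimum is not an error. The same total also has to serve the secondary outcomes, and uncorrected with 5% loss caesarean section alone needs about 516 (245 × 2 / 0.95), which is close to 524. The planned analysis is of adjusted relative risks with multiple imputation, which does not point to a continuity-corrected test. The Data management section also seeks consent to use birth outcomes after withdrawal, so actual loss may be below 5%. Finally, an abstract that omits attrition is ordinary condensation.

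Much of this stands. The corrected 77.8% should not be read as the power of the planned analysis, and the abstract's silence proves nothing by itself. But the uncorrected route explains neither 524 nor the printed rates: at 249 per arm it gives 7.51%, 27.3%, 25.2% and 3.68%, and none of these is printed. Imputation does not restore the information lost with missing outcomes, and better retention would not make the claimed allowance true. Nor is this a detail left to a fuller document, because the article states both the inputs and the result.

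**Conclusion.** The concern holds. The 524 equals the continuity-corrected requirement with complete outcomes, and the 5% allowance the article claims is not in it. On that method, the expected loss takes the primary outcome to 77.8% (2.2 points below the stated 80%) and three of the four secondary outcomes to between 77.6% and 78.0%; pre-eclampsia stays above 80%.

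This rests on equal allocation and on the inferred formula. The inference is strong, because four printed rates, including the unusually precise 7.35%, match it and do not match the calculations at 249 per arm. Without the correction, 524 tolerates up to about 9% loss for the primary outcome (1 − 476/524 = 9.2%). The error therefore lies in the stated derivation and power, not in a trial that is too small under every test.

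**What to change.** Keep 524 and correct the text in the Sample size section and the Abstract. Suggested wording: 524 women (262 per arm, continuity-corrected two-proportion test, two-sided alpha 0.05) gives 80% power to detect 15.5% against 7.35% with complete outcomes; with 5% loss (about 498 analysed), power is 77.8% with and 81.8% without continuity correction.

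Name the test assumed. Restate the secondary-outcome table for 498 analysed, giving power with and without the correction. If the corrected detectable rates are preferred for that table, they are 26.9% (caesarean section), 24.8% (induction), 6.1% (pre-eclampsia) and 3.35% (gestational diabetes).

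The cost is wording only: no added women and no change to the analysis. The stated power becomes about 2 points less favourable on the corrected method. The alternative, keeping both the corrected method and the 5% allowance, would mean a target of 552, or 28 more women.

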**Table Taba:** 

Outcome	Difference in Incidence	Difference Detected
Caesarean Section	39.1% to 27.2%	12%
Induction of labour	36.8% to 25.1%	12%
Pre-Eclampsia	14.1% to 6%	8%
Gestational Diabetes	10% to 3.5%	6.5%

### Data management

All information obtained from this study will remain strictly confidential. While the results of the study will be published, no data will be presented to allow the identification of individual women. Data will be stored in a locked filing cabinet or on password protected computer file, and accessible only by the study team.

We have previous experience recruiting women for lifestyle intervention trials in this setting [12] and will consider adding further sites as required. Women who withdraw from ongoing participation after randomisation will be asked for consent to utilise the data already collected prior to withdrawal, including birth outcomes where possible.

### Ethics approval

Approval to conduct this study has been obtained from the Women's and Children's Health Network (WCHN) Human Research Ethics Committee's (HREC) and local institutional approval at Women’s and Children’s Hospital, Flinders Medical Centre and the Lyell McEwin Hospital. Any amendments to the trial protocol will be notified in writing to each of the responsible HREC’s, research assistants, and clinicians involved in the study, and where relevant an amendment made to the trial registration.

A data and safety monitoring board (DSMB) will monitor efficacy (or futility) and adverse effects. Based on these considerations, the DSMB may recommend that the protocol be modified or that the GRoW trial be terminated. The DSMB will consist of experts in relevant obstetrics, neonatology and research methodology. All adverse events involving women and infants enrolled in the trial will be reviewed by a multidisciplinary committee, who will be blinded to treatment allocation, in order to clarify cause. These data will be made available for the Data Safety Monitoring Board.

## Discussion

This is a protocol for a randomised trial assessing whether the use of metformin in pregnancy, as an adjuvant therapy to dietary and lifestyle advice for women who are overweight or obese is effective in improving maternal, fetal and infant health outcomes. The findings of this trial will contribute to the currently available literature regarding the effect of metformin in pregnancy for women who are overweight and obese, [36, 37] and to the development of evidence based clinical practice guidelines.
